### Secondary outcomes

Secondary outcomes include:

(1) The change in LIBRA score. The LIBRA score has been validated among individuals in midlife and reflects an individual’s potential to reduce their risk on developing late-onset dementia.^52^ The LIBRA score consists of 12 currently known protective (ie, Mediterranean diet, low/moderate alcohol consumption, cognitive activity) and risk factors (ie, physical inactivity, smoking, CVD, hypertension, high cholesterol, diabetes mellitus, obesity, renal dysfunction, depression) for dementia and ranges from −5.9 (low risk for developing dementia) to 12.7 (high risk for developing dementia).

A one point increase in the LIBRA score is associated with a 19% higher risk for dementia.^52 60^ The definitions and corresponding scores for the three protective and ten risk factors for dementia are described in table 3.

**Table 3 T3:** Definition of risk and protective factors for dementia in the LIBRA score and corresponding scores

Modifiable risk factors		Definition	Score
Protective factors			
1	High cognitive activity	Score ≥50 points on the Cognitive Reserve Index questionnaire (leisure time activities) or hours of paid work ≥24 hours	−3.2
2	Mediterranean diet	MIND-diet score (0–14) =14 points	−1.7
3	Low/moderate alcohol consumption	Average number of glasses of alcohol a week ≤7 and number of glasses a day is: ≤3 glasses for women (no binge drinking), ≤4 glasses for men (no binge drinking)	−1.0
Risk factors			
4	Cardiovascular diseases	Presence of at least one of the follow diseases: history of angina pectoris, myocardial infarction, transient ischaemic attacks, stroke or peripheral arterial diseases	+1.0
5	Physical inactivity	Not fulfilling Dutch Norm for Physical activity defined as ≥150 min/week physical activity of moderate to vigorous intensity, measured with the SQUASH questionnaire	+1.1
6	Renal dysfunction	Estimated glomerular filtration rate ≤60 mL/min/1.73 m^2^	+1.1
7	Diabetes mellitus	Glucose (capillary blood) >7.0 mmol/L or HbA1c >53 mmol/mol	+1.3
8	High cholesterol	LDL >2.5 mmol/L or TC/HDL >5	+1.4
9	Smoking	Current smoker	+1.5
10	Obesity	BMI ≥30	+1.6
11	Hypertension	SBP >140 mmHg or DBP >90 mmHg	+1.6
12	Depression	Score ≥16 points on the Centre for Epidemiologic Studies Depression scale	+2.1

BMI, body mass index; DBP, diastolic blood pressure; HbA1c, haemoglobin A1C; HDL, high-density lipoproteins; LDL, low-density lipoproteins; LIBRA, lifestyle for brain health; MIND-diet, mediterranean-DASH diet intervention for neurodegenerative delay; SBP, systolic blood pressure; SQUASH, short questionnaire to assess health-enhancing physical activity; TC, total cholesterol.

(2) The change in the individual health behaviours, including physical activity (minutes of moderate to vigorous physical activity per week), diet (mediterranean-DASH diet intervention for neurodegenerative delay score; 0–14), alcohol consumption (number of glasses of alcohol per week), smoking behaviour (current smoker (yes/no) and number of cigarettes/cigars a day), cognitive activity (leisure-time cognitive activity score and number of hours paid work), loneliness (overall loneliness score; 0–6) and social activity (number of contacts per 2 weeks) and their stage of change over time. The stages of change are categorised into pre-contemplation (1), contemplation (2), preparation (3), action (4) and maintenance (5).^33^

(3) Changes in beliefs and attitudes with regard to DRR are measured using the Motivation to Change Lifestyle and Health Behaviour for DRR Scale (MCLHB-DRR scale).^61 62^ The MCLHB-DRR scale is based on the HBM,^32^ which explains health-related behaviours. Seven subscales of the HBM were included: perceived susceptibility, perceived severity, perceived benefits, perceives barriers, cues to action, general health motivation and self-efficacy. Participants are asked to rate all items on a 5-point Likert scale, ranging from strongly disagree (score=1) to strongly agree (score=5). A higher score on each subscale reflects a higher motivation to change their lifestyle and health behaviour for DRR. The Dutch version of the MCLHB-DRR scale, consisting of 23 items, has shown to be valid in the Dutch general population aged between 30 and 80 years old.^63^

(4) Percentage of participants that indicated in the questionnaire that they have followed up the tailor-made online lifestyle advice (‘On what risk factors did you receive lifestyle advice?’ and ‘Did you follow-up the tailor-made lifestyle advice since the last questionnaire (with regard to (risk factor))’?, but also the percentage of participants that indicated that they have followed up the advice to consult their General Practitioner (‘Did you have contact with your general practitioner after receiving feedback on the risk and protective factors?’).

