### Personal health profile

After completion of the baseline dementia risk assessment (including the data entry of the physical examination and laboratory measurements), a personal health profile is automatically provided in the personal account of the participants (My Demin). The personal health profile gives an overview of the presence of the risk and protective factors for dementia, without including the weight of the risk and protective factors. According to the Lifestyle for Brain Health (LIBRA) score, each risk and protective factor^19 52 53^ is categorised into one of the following categories: (1) room for improvement, (2) remember to manage well, (3) keep this up (see table 2). The ‘keep this up’ category represents factors that participants are currently managing well or diseases they do not have. The ‘room for improvement’ category represents the factors that could be improved by health behaviour change (eg, quit smoking, become more physical active, change diet, drink less alcohol). The category ‘remember to manage well’ is assigned when a risk factor (ie, cardiovascular diseases, hypertension, high cholesterol, diabetes mellitus, renal dysfunction and depression) is present, but the disease is managed well as participants have regular meetings with their general practitioner for disease control (diabetes mellitus) or use medication for disease management (cardiovascular diseases, hypertension, high cholesterol, renal dysfunction and depression) (see figure 1).

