### Tailor-made online lifestyle advice for dementia risk reduction

Participants also receive an online tailor-made lifestyle advice targeting risk factors associated with dementia and following the Dutch guidelines for a healthy diet, alcohol consumption, physical activity, diabetes mellitus, renal dysfunction and cardiovascular health including cholesterol levels and BMI.^54–58^ For each risk and protective factor, information is given about (1) the norm (cut-off point for not having this risk factor), (2) the association between the risk factor and dementia and (3) lifestyle advice how to tackle this factor. The online lifestyle advice was tailored to the participants based on (1) the presence of risk factors, (2) the strength of the association between the risk factors and dementia^19 52^ and (3) the stages of change of the health behaviour-related risk factors (physical inactivity, diet, alcohol consumption, smoking behaviour, cognitive activity, social activity). The stages of change are determined by asking ‘Which statement fits best for you?’, where each answer option reflects one of the following stages of change: pre-contemplation, contemplation, preparation, action and maintenance.^33^ It is known that participants who are in the preparation and action stage are more willing to change their health behaviour, therefore lifestyle advice for these factors are given first.^33^

In case medically relevant findings are found, including untreated diabetes mellitus (glucose ≥7.0 mmol/L or (glucose ≥6.1 mmol/L and HbA1C>53 mmol/mol)), untreated renal dysfunction (estimated glomerular filtration rate (eGFR) ≤60 mL/min/1.73 m^2^) and increased risk for developing CVD (CVD risk ≥10% according to the Dutch Systematic Coronary Risk Evaluation (SCORE) formula^59^), participants receive, in addition to the online tailor-made lifestyle advice, a separate message in their personal inbox with the recommendation to contact their general practitioner to verify the results and discuss whether treatment is needed.

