### Adverse events

The risk classification of this intervention is considered negligible, since only information and health advice is provided. Serious adverse events as a result of the intervention are not expected, thus no data safety and monitoring board is installed. Potential participants are informed about possible adverse events. For example, dementia risk assessment may help raising the awareness of their susceptibility in order to motivate health behaviour change,^32^ however, risk assessment could also have an unfavourable effect. Participants may become anxious about developing dementia and could experience more stress if they receive their health profile. Therefore, participants are clearly informed that the presence or absence of risk and protective factors is not a reassurance that they will develop dementia later in life. Furthermore, participants are informed that there is the possibility that unexpected medical findings can be found. In this case, participants receive a separate message in their personal inbox with the recommendation to contact their general practitioner to verify the results (hypertension, high cholesterol, renal dysfunction, diabetes) and discuss whether treatment is needed. Participants may consider online risk assessment as a privacy risk. In this study, all personal information is kept separately from the research data, and participants use a SMS-tan code to login in their personal account.

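### The general practitioner item in secondary outcome (4) records any contact after feedback, so it does not measure whether advised participants followed the advice

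*Protocol article*

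**What the plan says.** The protocol article's section on secondary outcomes, item (4), describes the outcome as "the percentage of participants that indicated that they have followed up the advice to consult their General Practitioner". The question given for it is "Did you have contact with your general practitioner after receiving feedback on the risk and protective factors".

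The other half of item (4), on lifestyle advice, is built differently. It first asks "On what risk factors did you receive lifestyle advice" and then asks, factor by factor, whether that advice was followed in the period since the previous questionnaire.

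Two sections describe who is told to contact the GP:

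- The section on tailor-made online lifestyle advice begins "In case medically relevant findings are found, including untreated diabetes mellitus", goes on to untreated renal dysfunction and a cardiovascular risk of 10% or more, and says that people in this group are sent "a separate message in their personal inbox with the recommendation to contact their general practitioner to verify the results".
- The Adverse events section describes the same kind of message for unexpected findings, but its list is different: "to verify the results (hypertension, high cholesterol, renal dysfunction, diabetes".

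The Personal health profile section shows that some GP contact is routine. It describes well-managed diabetes as the case where "participants have regular meetings with their general practitioner for disease control (diabetes mellitus". The article gives no rate of GP contact, does not say what share of participants will be sent the message, and does not state the denominator for this percentage.

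**The concern.** The label is about following a specific piece of advice. The item is about any contact after an event (feedback) that every participant with a completed baseline assessment experiences. Two gaps follow.

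1. **Numerator.** A participant who was sent the message, ignored it, and later saw the GP about something else answers yes and is counted as having followed the advice.
2. **Denominator.** The wording speaks of participants, while only some were advised. If everyone is counted, people with nothing to comply with enter the percentage, as apparent compliers if they happened to see a GP and as apparent non-compliers if they did not.

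Contacting the GP to verify a relevant finding is the one GP action the programme recommends, and compliance is one of four listed secondary outcomes. At stake is whether the trial can say how often people with such a finding had it followed up because the programme told them to.

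**Working it through.** The article states no figure for this outcome, so there is none to reproduce. The check concerns the direction and possible size of the error.

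**Inputs.** None of these is in the article; all are assumptions.

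- a = share of participants sent the GP message
- c = true compliance: the share of those advised who contact the GP because of the message
- b = probability of GP contact for another reason within the period the item covers, taken as independent of c and equal in both groups

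**Advised participants only.**

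Measured yes = c + (1 − c)b. Excess over c = (1 − c)b, which is positive whenever b > 0 and c < 1.

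With c = 0.50:

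| b | measured | excess |
|---|---|---|
| 0.12 | 0.50 + 0.50 × 0.12 = 0.56 | 6 points |
| 0.20 | 0.50 + 0.50 × 0.20 = 0.60 | 10 points |
| 0.40 | 0.50 + 0.50 × 0.40 = 0.70 | 20 points |
| 0.60 | 0.50 + 0.50 × 0.60 = 0.80 | 30 points |

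The 12% row reflects the recall window. If unrelated contact is 40% over a year and spread evenly, the three-month figure is 1 − 0.60^(1/4) = 0.12. The article does not give the window for this item.

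**All participants.**

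Measured yes = a[c + (1 − c)b] + (1 − a)b.

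This exceeds c only if b > c(1 − a)/(1 − ac). With a = 0.3 and c = 0.5, the break-even is 0.35/0.85 = 0.41.

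- b = 0.3: 0.3 × 0.65 + 0.7 × 0.3 = 0.405, which is 9.5 points below c.
- b = 0.5: 0.3 × 0.75 + 0.7 × 0.5 = 0.575, which is 7.5 points above c.

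Over a grid of 48 combinations (a = 0.1, 0.3, 0.5, 0.8; c = 0.3, 0.5, 0.7; b = 0.1, 0.3, 0.5, 0.7), the all-participant percentage lies above c in 27 and below c in 21. The differences run from −54 to +47 points.

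**In heads, for the planned 378 participants** (a = 20%, c = 50%, b = 40%):

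- Advised: 0.20 × 378 ≈ 76. Of these, 38 act on the advice and 0.40 × 38 ≈ 15 of the rest have unrelated contact, so 53/76 = 70% say yes.
- Not advised: 302, of whom 0.40 × 302 ≈ 121 say yes.
- Everyone: (53 + 121)/378 = 46%.

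The 46% is below the 50% compliance among the advised, yet far above the 38/378 = 10% of all participants who acted on the advice. Against that 10%, the excess is b(1 − ac) = 0.40 × 0.90 = 36 points and is never negative. The direction therefore depends on which quantity the percentage is taken to estimate, and the article does not settle that.

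**The case against.** The strongest reply is that a journal article condenses the questionnaire and leaves exact denominators to the analysis plan. Only someone who was advised can follow advice, so an advised-only denominator is a natural reading. The section on dementia risk assessment says the online questionnaire has skip rules, so the item may be shown only to message recipients or be followed by a question on the reason for contact. The English item is presumably translated from Dutch. All the rates above are assumed, and a three-month window would shrink the error. GP contact is not among the outcomes named under Statistical analyses.

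Much of this stands. It rules out three stronger conclusions that a reader might draw:

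- *The outcome necessarily overstates compliance.* This holds among advised participants. It does not hold when an all-participant percentage is read as compliance among the advised, as 46% against 50% shows.
- *The figure is mostly background GP contact.* This depends entirely on assumed rates.
- *A treated diabetic attending a routine check is counted as compliant.* On the list in the lifestyle advice section, the diabetes trigger is untreated disease, so this person counts only if non-recipients are in the percentage, or if the broader wording under Adverse events decides who is advised.

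What the reply does not remove is the numerator problem. An analysis plan can restrict the denominator, and routing can restrict who sees the question. Neither recovers a reason for contact if that reason was not asked, and the item as quoted does not ask it. The lifestyle half of the same outcome shows that tying follow-up to advice received was feasible.

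**Conclusion.** The concern holds as a mismatch between label and measure. As quoted, the item counts any GP contact after feedback, while the advice it is meant to track goes only to participants sent the separate message.

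Among those advised, apparent compliance is too high by (1 − c)b: between 6 and 30 points for an assumed true compliance of 50% and unrelated contact of 12% to 60%. This rests on unrelated contact being independent of compliance. Over all participants, the percentage mixes in people who were never advised and may lie on either side of compliance among the advised, so no fixed direction can be claimed.

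The two trigger lists add to the difficulty, because they define who was advised and they differ: cardiovascular risk appears in one, hypertension and high cholesterol in the other, and only one limits diabetes and renal dysfunction to untreated disease. The first list is introduced as inclusive, so it may not be complete.

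Severity is minor. This is one self-reported half of one secondary outcome. The primary outcome and the sample size do not depend on it.

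**What to change.** 1. State that the denominator is the participants who were sent the GP message. They should be identifiable from the messages the system placed in the My Demin inbox or, failing that, from the baseline findings in the electronic case report form.
2. Reword the item, or add one follow-up question, so that it asks whether the GP was contacted about the Demin results. State the period it covers.
3. Report GP contact among participants who were not sent the message separately, as background.
4. For answers already collected with the current item, restrict the percentage to message recipients and state that unrelated contacts are included.
5. Reconcile the trigger lists in the lifestyle advice and Adverse events sections, so that the advised group is defined once.

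The cost is one changed or added questionnaire item, a link to the message records, and a short clarification of the text. No extra participants or visits are needed.

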### Statistical analyses

First, descriptive characteristics will be explored. The difference in uptake between the two recruitment strategies will be examined using multilevel logistic regression analyses in order to correct for clustering at memory clinic level. We will calculate the percentage with the corresponding 95% CI and use an alpha of 0.05 to test statistical significance.

The effectiveness of the online tailor-made lifestyle programme for DRR will be determined by, first comparing the change in LIBRA score, the individual risk factors and the MCLHB-DRR score between the active and passive recruitment strategy, and second comparing participants of the Demin study (active and passive recruitment strategy) to a control group consisting of Lifelines participants (large population-based cohort study (n>167 000)) (www.lifelines.nl)^64^ in outcome. Lifelines participants (age 40–60 years) with a parent with dementia will be matched (using propensity scores) on non-modifiable risk factors (age, gender and education) for dementia to participants of the Demin. Subsequently, multilevel analyses will be performed to examine the change in the LIBRA score and the individual health behaviours over time. In addition, possible confounding and interaction effects will be identified and corrected for in the analysis (eg, health literacy). We will calculate relative risks with 95% CIs and use an alpha of 0.05 to test significance.

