**Methods and analysis:**

Demin is a cluster randomised controlled trial, aiming to include 21 memory clinics of which 13 will be randomly allocated to the passive (poster and flyer in a waiting room) and 8 to the active recruitment strategy (additional personal invitation by members of the team of the memory clinic). We aim to recruit 378 participants (40–60 years) with a parent who is recently diagnosed with Alzheimer’s disease or vascular dementia at one of the participating memory clinics. All participants receive a dementia risk assessment (online questionnaire, physical examination and blood sample) and subsequently an online tailor-made lifestyle advice regarding protective (Mediterranean diet, low/moderate alcohol consumption and high cognitive activity) and risk factors (physical inactivity, smoking, loneliness, cardiovascular diseases (CVD), hypertension, high cholesterol, diabetes, obesity, renal dysfunction and depression) for dementia. The primary outcome is the difference in uptake between the two recruitment strategies. Secondary outcomes are change(s) in (1) the Lifestyle for Brain Health score, (2) individual health behaviours, (3) health beliefs and attitudes towards DRR and (4) compliance to the tailor-made lifestyle advice. Outcomes will be measured at 3, 6, 9 and 12 months after baseline. The effectiveness of this online tailor-made lifestyle programme will be evaluated by comparing Demin participants to a matched control group (lifelines cohort).

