The first challenge of health behaviour change interventions is to achieve a high level of uptake for screening (eg, assessing risk and protective factors for dementia), reflecting the willingness to participate. A systematic review identified a large variation in uptake in health checks and lifestyle intervention programmes,^37^ depending on the type of recruitment strategy. The two main types of strategies for recruitment are the active and passive recruitment strategy. Active recruitment involves a personal invitation by the project staff and healthcare providers (eg, proactive) and passive recruitment involves recruitment of participants through various channels such as flyers and advertisements (eg, reactive).^38^ The most effective recruitment strategy is a proactive referral from a healthcare provider, while displaying posters and flyers showed to be less effective.^39 40^ Uptake also depends on other factors as described in social cognition models (eg, knowledge, perceived susceptibility and severity, facilitators, benefits and barriers and attitude towards such interventions).^32–36^ These factors are essential and useful to make a well-informed decision about dementia risk assessment, considering the possible benefits and harms. Therefore, information on dementia, the risk and protective factors for dementia, heritability and how to tackle risk and protective factors for dementia are important factors in the development of a web-based intervention. A previous study showed that the majority of the Dutch general population is unaware of the relationship between modifiable risk factors and brain health, particularly regarding major cardiovascular risk factors (eg, hypertension, hypercholesterolemia and coronary heart disease).^41^ It is shown that this lack of knowledge is a barrier to the uptake and maintenance of healthy behaviours for middle-aged individuals.^42^ Having a parent who is recently diagnosed with AD or VD could have led to an increased knowledge on dementia and risk perception.^13^ Therefore, middle-aged descendants of recently diagnosed people with AD or VD might be receptive to assess their risk and motivated to adopt a healthier lifestyle as they just realised their (familial) risk.^13 43^ Although we expect that the uptake in the active recruitment strategy will be higher compared with the passive recruitment strategy, participants recruited via the passive recruitment strategy might be more intrinsically motivated to adopt and maintain their healthy lifestyle and less likely to drop out of the study.

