## Methods and analysis

### Study setting and design

This study is a pragmatic cluster randomised controlled trial (RCT), including 21 participating memory clinics in the Netherlands who are randomly allocated to a passive or active recruitment of participants. Memory clinics allocated to the active recruitment strategy invite potential participants face-to-face by a member of the team of the memory clinic to participate in the tailor-made online lifestyle programme for DRR (also called the Demin study), next to posters and flyers that are placed in the waiting room of the memory clinic. Memory clinics allocated to the passive recruitment strategy, do not invite potential participants proactively, but invite potential participants to participate in the Demin study by posters and flyers that are placed in the waiting room of the memory clinic.

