Patients with AD or VD (or their caregivers) receive an envelope either at the registration desk of the memory clinic or after the consult of the patient (only with active recruitment). This envelope is addressed to the middle-aged descendants of patients with recently diagnosed AD or VD and includes a patient information form (PIF) with information about the content of the study, the advantages and disadvantages of study participation and how potential participants can participate. Potential participants (one family member per patient) are asked to register themselves (eg, making an account) on the Demin website (www.demin.nl), by using the memory clinic specific login access code, which is reported on the front page of the PIF and represents the memory clinic in which the parent was diagnosed. The decision to participate is confirmed by the participants by signing the online informed consent form (electronic signature by using SMS-tan). After signing this form, individuals from both recruitment strategies are able to log in to their personalised website ‘My Demin’ and continue the intervention in an equal manner. The personalised website ‘My Demin’ is secured and only accessible for the participant by logging in with their personal email address, password and SMS-tan code. ‘My Demin’ contains the following information: (1) My personal (account) information, (2) Message inbox, (3) My online questionnaires, and (4) My personal health profile including online tailor-made lifestyle advice. After participants have completed the online questionnaire, they automatically receive a message with a request to make an appointment for physical examination including a fasting blood sample. Moreover, participants can invite siblings to participate in the study in ‘My Demin’.

The functionalities provided by the Demin website are based on the literature and input we received from people with a parent with dementia (focus group discussions).

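### The first of the two comparisons listed for programme effectiveness, active against passive recruits, cannot establish effectiveness because both groups receive the same programme

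*Protocol article*

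**What the plan says.** All references are to the protocol article.

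- **Statistical analyses**, first comparison: the programme's effectiveness is to be determined first by "comparing the change in LIBRA score, the individual risk factors and the MCLHB-DRR score between the active and passive recruitment strategy".
- **Statistical analyses**, second comparison: "second comparing participants of the Demin study (active and passive recruitment strategy) to a control group consisting of Lifelines participants". The Lifelines participants are aged 40–60, have a parent with dementia, and are matched by propensity score on age, gender and education.
- **Study setting and design**, what is randomised: memory clinics are "randomly allocated to a passive or active recruitment of participants".
- **Study setting and design**, what happens next: descendants register and consent on the website themselves. After consent, people from both strategies "continue the intervention in an equal manner".
- **Introduction**: uptake is expected to be higher with active recruitment, but "participants recruited via the passive recruitment strategy might be more intrinsically motivated to adopt and maintain their healthy lifestyle", and they may be less likely to drop out.
- **Abstract**, Methods and analysis: everyone who takes part receives the risk assessment and then the tailored advice. Effectiveness "will be evaluated by comparing Demin participants to a matched control group (lifelines cohort"). No other effectiveness comparison is named there.

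**The concern.** An effectiveness comparison needs one group that has the programme and one that does not. The first listed comparison has no group without it. It is also made among people who chose to enrol after their clinic had been allocated, so randomising the clinics does not make the two sets of participants comparable.

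Effectiveness is one of the study's two stated aims, alongside uptake. As the section is worded, a null active-passive difference could be read as evidence against a programme that works in both groups. A difference produced by who signed up could be read as evidence that the programme works. The section also gives no rule for the case where its two comparisons disagree. A null first comparison beside a favourable Lifelines comparison would look like conflicting evidence, although the first says nothing about a shared effect.

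**Working it through.** **1. The plan's own figure, and what it covers.** The inputs are in Sample size calculations: uptake 30% vs 50%, power 80%, alpha 0.05, ICC 0.05, cluster sizes 15 and 25.

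- Two proportions, two-sided, no continuity correction: n = (1.96 × √(2 × 0.4 × 0.6) + 0.8416 × √(0.3 × 0.7 + 0.5 × 0.5))² / 0.20² = 93 per group, against 94 stated.
- m = (15² + 25²)/(15 + 25) = 21.25. Inflation factor = 1 + 20.25 × 0.05 = 2.0125. 188 × 2.0125 = 378.35, against 378 stated.

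The figure reproduces. It is built on uptake alone, so nothing below alters it.

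**2. What each comparison estimates.** Write a participant's change as u + τ, where u is the change that would occur without the programme and τ is the person's response to it.

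- Active minus passive = [mean u, active enrollees − mean u, passive enrollees] + [mean τ, active enrollees − mean τ, passive enrollees].
- Demin minus Lifelines = mean τ among Demin participants + [mean u, Demin − mean u, Lifelines].

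If τ is the same for everyone, it cancels from the first line. If τ varies, the first line contains only a difference in average response between two sets of enrollees, mixed with their difference in u. Neither case gives the average response itself. The second line does contain it, together with a confounding term, because that comparison is not randomised.

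**3. Simulation of a common effect.** Both groups receive the same effect, and motivation has no influence on change. The model is assumed; only the 50% and 30% uptake come from the protocol.

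| True effect on LIBRA change | Active minus passive |
|---|---|
| 0 | −0.003 |
| −0.5 | 0.001 |
| −1.0 | −0.012 |
| −2.0 | 0.001 |

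The contrast is zero apart from simulation noise, whether the programme does nothing or lowers LIBRA by 2 points.

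**4. Illustration of selection.** The documents give no correlation between motivation and change and no SD of LIBRA change, so these inputs are assumptions.

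- *Strict threshold.* The most motivated 50% enrol under active and the most motivated 30% under passive recruitment, on a standard normal trait. Mean motivation is φ(0)/0.5 = 0.798 SD and φ(0.524)/0.3 = 1.159 SD, a difference of 0.361 SD. With an assumed correlation of 0.3 and an SD of change of 1.5, the bias is 0.361 × 0.3 × 1.5 = 0.16 LIBRA points in favour of passive recruitment. Correlations of 0.2 and 0.4 give 0.11 and 0.22.
- *Noisy selection.* Enrolment depends on motivation plus equal random noise, and change improves by 0.5 points per SD of motivation. Simulated active minus passive is 0.125, 0.132, 0.124 and 0.137 for true effects of 0, −0.5, −1.0 and −2.0. The difference is about the same whether or not the programme works.

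**The case against.** The strongest reply is that the programme is not judged on this contrast alone. The same sentence adds the Lifelines comparison, which does have people outside the programme, and the abstract puts that one forward. This stands. A reader might infer that effectiveness rests wholly on active against passive; the text does not support that, and the point is confined to the first of two comparisons. The second comparison does not, however, repair the first.

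A reader might also infer that the contrast can never depend on the programme effect. That is too strong. It holds only if response is unrelated to who enrols and how they were invited. The protocol orders its advice by stage of change and expects motivation to matter for maintaining a healthy lifestyle, so response may well vary. The contrast would then carry some trace of the programme, but still not a measure of whether it works.

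The size of the bias is assumed, and strict threshold selection is an extreme case. Suppose an SD of 1.5, 189 per group, no dropout, and the 2.01 inflation factor carried over to this outcome. The standard error is then 1.5 × √(2/189) × √2.01 = 0.22. A bias of 0.16 is about 0.74 standard errors and would give two-sided p < 0.05 about 11–12% of the time instead of 5%. The LIBRA range is 18.6 points (−5.9 to 12.7). This does not demonstrate a large false-positive risk, and the point does not depend on one.

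Two further inferences go beyond the text. The Statistical analyses section does not call this contrast randomised evidence of effectiveness; the intervention and control labels in Randomisation of memory clinics refer to recruitment strategy. And an abstract that names only the Lifelines comparison is ordinary condensation, not a contradiction.

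Finally, comparing change by recruitment route has a proper use: the Introduction asks whether passive recruits, though fewer, sustain change better. That supports keeping the comparison under a different label. The planned correction for confounding may reduce differences between enrollees, but it cannot supply a group without the programme.

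**Conclusion.** The point holds for the first listed comparison only. Because both groups receive the same programme, that comparison cannot establish effectiveness: an effect shared by all participants cancels, and anything left reflects who enrolled or how response varies with who enrolled. This follows from the design as described and needs no numerical assumption.

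The selection effect of about 0.1 to 0.2 LIBRA points is an illustration under assumed inputs, not an estimate. The protocol itself offers the expected direction only tentatively, as something that might be so.

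This should be corrected, since it affects what the trial can conclude on one of its two aims. It leaves the primary uptake analysis, the randomisation, the data collection and the 378 participants as they are.

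**What to change.** In Statistical analyses, take the active-passive contrast out of the definition of programme effectiveness. Keep it as a secondary comparison of change in LIBRA, individual risk factors and MCLHB-DRR between participants recruited by the two routes, and state that it is subject to selection after randomisation. Rest effectiveness conclusions on the matched Lifelines comparison, labelled non-randomised, in line with the abstract.

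The cost is a change of wording. The sponsor gives up the active-passive contrast as evidence of effectiveness. No analysis is lost, and no sample size or procedure changes.
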